**Hypotheses:**

**1)** Biweekly β-D-glucan surveillance will identify SICU patients with an invasive fungal infection (IFI) before clinical signs or symptoms develop.

1. Anidulafungin initiated in response to a positive β-D-glucan test (i.e. preemptive therapy) will be well tolerated, safe, and effectively treat patients early, before advanced infection is established.
2. Peripheral blood gene expression signatures obtained serially from at-risk patients can predict early IC.

**Study Design:** Single center, randomized, non-blinded, parallel group, comparative study.

**Sample Size:** 100 subjects; 75 in the active surveillance/preemptive therapy arm and 25 in the usual care arm.

**Study Population:** Adult patients admitted to Duke University Medical Center SICU at-risk for the development of IC.

**Study Drug:** Intravenous anidulafungin initiated in response to a positive β-D-glucan test for subjects in the active surveillance/preemtpive arm. Preemptive treatment will continue for at least 14 days or until ICU discharge (maximum 28 days), which ever is longer.

**Efficacy:** IFI assessments will be made weekly and at SICU discharge.

**Safety:** A data safety monitoring board will review adverse events every 4 months.

**Statistics:** β-D-glucan test characteristics will be described using sensitivity, specificity, positive and negative predictive values. The proportions of patients developing proven or probable IC in each group will be compared using Fisher’s exact test. The prevalence of treatment emergent adverse events will be described using summary statistics. For gene expression analysis, we will designate subjects diagnosed with a *Candida* bloodstream infection as case patients and those who remained uninfected and had negative B-D-glucan testing as controls. Decision tree analysis will be used to develop predictive signatures for candidemia versus no infection.

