**All Subjects**

The following procedures will be performed for all study subjects for the duration of the SICU stay:

- Serum red-top BDG and a PAX Gene tubes will be obtained 2 times/week (generally Monday and Thursdays) with the routine early morning blood work by the SICU nursing staff. Both phlebotomy tubes will be sent directly to the Duke Clinical Microbiology Laboratory. BDG results will be made available in real-time (within 24–72 hours) via a phone call directly to the clinician (surgical house staff and unit pharmacist) caring for the study subject assigned to preemptive therapy. BDG specimens obtained from patients assigned to empiric therapy (standard care) will be batched and tested at the end of study and the clinicians will not be made aware of the results. All RNA analyses will also be performed retrospectively for research purposes only.

*Patients in the active surveillance/preemptive therapy arm may have BDG testing performed on other days if the providers feel that the result would immediately impact initiation of antifungal therapy. The test will be available daily Monday through Friday.

- IFI assessments will be made weekly (EORTC/MSG criteria for proven or probable IFI will be applied [**Tables 3 & 4**]) and documented on the CRF.
- Supporting evidence of IFI obtained as part of routine care will be recorded weekly (i.e. routine laboratory testing, microbiology and blood culture results, imaging studies, biopsy reports) and documented on the CRF.
- Clinical risk factors for IC will be documented weekly (**Table 1**) and documented on the CRF.
- Factors known to be associated with false positive BDG tests will be documented weekly (**Table 2**) and documented on the CRF.
- Concomitant antimicrobials and immunosuppressive drugs will be documented weekly on the CRF.
- AEs will be recorded weekly and documented on a dedicated CRF.

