**WHILE ON PREEMPTIVE THERAPY**

- Serum for BDG will be collected every other day until negative. Once the test becomes negative, twice weekly surveillance will be resumed.
- Complete physical examination including vital signs once weekly.
- Assessment for breakthrough IFI as defined by EORTC/MSG criteria.
- LFTs once weekly.
- AEs will be recorded and drug tolerability assessed at the time of the physical examination.
- PAX Gene tubes will continue to be obtained 2 times/week.
- Concomitant medications will be documented weekly.

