**Secondary Endpoints**

1. Prevalence of IC by treatment group (i.e., preemptive therapy versus standard care).
2. Duration of SICU stay by treatment group.
3. Number febrile days by treatment group.
4. Antifungal drug utilization by treatment group.
5. Overall mortality rate between treatment arms at SICU and hospital discharge.
6. Response to preemptive or empiric antifungal therapy will be assessed.
7. Fungal colonization rate by group at baseline, at the end of antifungal therapy, and at SICU discharge.
8. Susceptibility of fungal pathogens identified (if any).
9. Number of breakthrough IFIs by group.
10. Number of premature withdrawals from assigned strategy.
11. Costs (antifungal drugs + diagnostic testing) by group.
12. Gene expression signatures related to early candidemia (prior to blood culture positivity) and late candidemia (after blood culture positivity) and no candidemia (negative blood culture and negative B-D-glucan testing).

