Initial signature development cohort: RNA from patients with blood cultures growing *Candida* and an equal number of patients with negative blood cultures and negative BDG testing (controls) will be chosen for signature development. A decision tree approach used previously by our group will be used to find gene expression patterns that are correlated with candidemia to determine the predictive capability of those gene patterns as a diagnostic test(28;29). Once we identify a large number (100-300) of gene expression patterns that significantly correlate with the illness classification in our initial cohort, we will then identify the best combination of 3-5 patterns for discriminating between those with candidemia and those with no infection. Once the best expression patterns are identified, we will perform cross validation analysis in which we construct a decision tree with the best gene patterns using all of the samples except for one “held out” sample. We can then use the decision tree model to predict the classification of the “held out” sample as an honest test of the accuracy of our predictive model and to guard against over-fitting. We plan to define host gene expression patterns in response to candidemia using an initial cohort of up to 30 persons with candidemia and up to 30 persons with no infection. This sample size has 90% power to detect at least a 2-fold change in expression levels in the 70% least variable genes with an alpha of 0.001(30). After establishing robust gene expression signatures that classify individuals as having a “candidemia” or “no infection” we will test the generalizability of these profiles on the remaining patients presenting to the intensive care unit at risk for invasive candidiasis. We will not know beforehand the etiology of their symptoms.

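### The gene-signature cross-validation starts only after the patterns have been chosen on the whole cohort, so its accuracy is inflated even when no gene carries signal; several arrays per patient, if used, would add a second leak.

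*Protocol*

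**What the plan says.** The RNA Analyses text under Statistical Analyses sets out a fixed order of steps.

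1. Screen for 100-300 "gene expression patterns that significantly correlate with the illness classification in our initial cohort".
2. From these, "we will then identify the best combination of 3-5 patterns for discriminating between those with candidemia and those with no infection".
3. Validate, and only at this stage: "Once the best expression patterns are identified, we will perform cross validation analysis". The rule for each fold of that validation is stated as follows: "we construct a decision tree with the best gene patterns using all of the samples except for one". The tree then classifies the sample left out.

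The protocol presents step 3 as an honest check of accuracy and a protection against over-fitting. A later test of the signature on the remaining ICU patients is also planned.

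The development cohort is counted in persons, up to 30 with candidemia and up to 30 without infection. The power statement rests on that count.

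RNA collection is serial. Under All Subjects: "Serum red-top BDG and a PAX Gene tubes will be obtained 2 times/week". Under While on Preemptive Therapy: "PAX Gene tubes will continue to be obtained 2 times/week". The third hypothesis in the synopsis is that "Peripheral blood gene expression signatures obtained serially from at-risk patients can predict early IC", and secondary endpoint 12 separates early from late candidemia according to blood culture positivity. The protocol does not say how many arrays per patient enter the development set.

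**The concern.** Cross-validation estimates accuracy without bias only if the left-out unit had no part in building the model. Here the most data-hungry part of model building, the search over a whole microarray for patterns that separate the classes, uses every label, including the one to be predicted later. Only the last and smallest part, the tree on 3-5 chosen patterns, is refitted without the held-out sample. Patterns that separate the groups by chance in the full cohort will go on doing so for the held-out sample, because that sample helped to make them look good.

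A second leak is possible. If a patient contributes several arrays, leaving out one of them keeps the others in training under the same label. The model can then recognise the patient instead of the infection.

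At stake is whether a signature with no diagnostic value is reported as predictive of candidemia on the strength of a figure described as honest.

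**Working it through.** **The plan's own figure.** The protocol claims 90% power for a 2-fold change (1 unit on the log2 scale) with 30 versus 30 persons at alpha 0.001. By the normal approximation, power = Phi(1/(SD x sqrt(2/30)) - z(0.9995)). Solving for 90% gives SD = 1/((3.291 + 1.282) x sqrt(2/30)) = 0.847. An SD of 0.7 gives 98.8% and an SD of 1.0 gives 72.0%. The protocol does not give the SD, so the 90% can be neither confirmed nor refuted. It concerns detection of single genes and says nothing about the accuracy of the signature.

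**Null simulation of the validation rule.** All genes are pure noise, so true accuracy is 0.50.

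- From the protocol: up to 30 per group with equal numbers, selection of 3-5 patterns (5 used), a decision tree, and one sample left out.
- Assumed: 3,000 independent genes, ranking by absolute t statistic, tree depth 2, 10 per group as a smaller case, and 3 arrays per person where serial samples are modelled.
- Serial model: expression = sqrt(rho) x patient effect + sqrt(1 - rho) x noise, with rho = 0.3, 0.6 or 0.8.
- Simplification: the 100-300 screen followed by the 3-5 choice is collapsed into one step, the top 5 genes.

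Mean cross-validated accuracy (where three values appear, they are for rho = 0.3 / 0.6 / 0.8):

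| Arrays per person | Selection | Left out | 10 per group | 30 per group |
|---|---|---|---|---|
| 1 | before the loop (as written) | one sample | 0.75 | 0.66 |
| 1 | inside each fold | one sample | 0.47 | 0.48 |
| 3 | before the loop | whole patient | 0.70 / 0.74 / 0.76 | 0.62 / 0.65 / 0.64 |
| 3 | inside each fold | one sample | 0.60 / 0.73 / 0.79 | 0.54 / 0.63 / 0.63 |
| 3 | inside each fold | whole patient | 0.46 / 0.45 / 0.49 | 0.48 / 0.52 / 0.54 |

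Monte Carlo standard errors are about 0.01 to 0.04.

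**Reading the table.**

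- Rows 1 and 2: the order of steps alone adds 0.75 - 0.47 = 0.28 at 10 per group and 0.66 - 0.48 = 0.18 at 30. No repeated sampling is needed.
- Row 3: holding out the whole patient does not cure this while selection stays outside the loop.
- Row 4: with selection corrected, several arrays per patient still inflate accuracy. At 30 per group and rho = 0.3 the excess (0.54, standard error 0.036) cannot be told from chance.
- Row 5: both corrections together return accuracy to about chance.

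**Sensitivity to the classifier.** With 2,000 genes and a majority vote of the best 5 in place of the tree, the written order with one array per person gave about 0.94 at 10 per group and 0.77 at 30. For the second leak alone (2 arrays, rho = 0.5, selection inside the loop), leaving out a sample versus a patient gave 0.65 versus 0.50 at 10 per group. At 30 per group, one run gave 0.62 versus 0.47 and another, of only 10 replicates, 0.54 versus 0.46. The direction is stable and the size is not.

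**The case against.** The strongest objection concerns repeated samples. Twice-weekly collection of tubes is not the same as hybridising several arrays per patient. The protocol says only that selected patients will be hybridised, and it counts the development cohort and its power in persons. On the plainest reading there is one array per person, and leaving out a sample is then the same as leaving out a patient. Endpoint 12 does not settle the matter. Early and late samples could come from different patients, or be modelled as separate classes, in which case a patient's two arrays would not share a label. This stands. A reader might infer from the serial sampling that leakage between arrays of one patient is built into the plan. The protocol does not support that, and the second leak remains conditional.

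It can also be said that fold structure belongs in an analysis plan, which is not at hand. That is fair for the number of arrays per patient. It does not cover the order of selection and validation, which the protocol itself fixes.

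The planned test on the remaining patients is a real but partial check. It may expose a worthless signature later. It does not make the cross-validated accuracy honest, and each case used for development is one fewer left for that test.

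Finally, this is the last of 12 secondary endpoints, so the main feasibility and safety conclusions are untouched.

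**Conclusion.** The point holds for the rule as written. Patterns are selected on the full cohort before any sample is left out, so the cross-validated accuracy is biased upward and cannot be called an honest test. With one array per person and no signal, the tree simulation gave 0.66 at 30 per group and 0.75 at 10, against 0.50 by chance.

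The patient-level leak is a conditional addition. It applies only if more than one array per patient enters the development set, which serial collection and endpoint 12 make possible but the protocol does not state. A reader might also infer that holding out whole patients would be enough; row 3 of the table shows that it would not.

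The sizes rest on assumed gene count, classifier, within-patient correlation, arrays per patient and number of cases, none of which the protocol fixes beyond naming a decision tree and an upper limit of 30 per group. The upward direction of the selection bias does not rest on them.

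**What to change.** In the RNA Analyses text, replace the validation sentences with a rule to this effect: *in each fold, all arrays from one patient are left out; the screen for 100-300 patterns, the choice of the best 3-5 and the fitting of the tree are all repeated on the remaining patients; the left-out patient is then classified, and accuracy is reported per patient.*

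State how many arrays per patient enter the development set. If it is one, patient grouping changes nothing and the nested selection is the whole correction. If early and late arrays from the same case are used, say whether they form one class or two.

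The cost is a few sentences, a grouping variable and more computing time, with no extra patients, samples or assays. The reported accuracy will be lower. The chosen patterns may also differ from fold to fold, so the figure describes the selection procedure and not one fixed signature; the final signature is still built on the whole cohort and carried to the planned test on the remaining patients.

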**INTRODUCTION**

**Epidemiology of Invasive Candidiasis**

Fungal infections are devastating to human health and have lethal consequences for both immunocompromised and critically ill patients in the Intensive Care Unit. *Candida* species are now the 4^th^ most common cause of bloodstream infection in the United States (1), with the vast majority of these infections being nosocomially acquired(2). Most *Candida* blood stream infections (BSIs) are due to *C. albicans* followed in frequency by *C. glabrata*, a species that is generally less susceptible to traditional antifungal therapy (i.e., fluconazole). Despite the availability of newer antifungal drugs, the mortality attributable to invasive candidiasis (IC) remains extremely high (3). One reason that IC is so devastating is the difficulty in establishing a timely diagnosis. The clinical presentation of IC is highly variable and nonspecific, and standard blood culture is notoriously insensitive. In addition to the clinical impact, IC is a burden on the healthcare system, with estimates of increased costs on the order of $40,000 US dollars per episode(4;5).

Patients in the ICU have a higher incidence of *Candida* BSI as compared to those on general medical/surgical wards(1). Given that IC carries such a high associated morbidity, mortality, and cost, prophylactic antifungal therapy has been proposed as a way to prevent disease in high-risk patient populations. Azoles and polyenes have both been studied as prophylaxis in the ICU setting and were shown to decrease the incidence IFIs without impacting overall mortality(6-10). Individual prophylaxis studies, however, have varied widely with regard to patient selection and antifungal regimen. No consensus on the optimal preventative strategy currently exists, but experts have advocated some form of antifungal prophylaxis in situations where the rate of IC is expected to approach 10%(11).

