**STATISTICAL METHODOLOGY**

**Sample Size**

Targeted enrollment is 100 adult SICU patients. This study will not be powered to show a difference in the efficacy of preemptive management versus standard care due to single center population constraints in addition to cost limitations. Sample size calculations were therefore based on the number of adult patients expected to be admitted to the SICU over a 1 year period who are likely to meet inclusion criteria (n=700). Based on prior experience, it is reasonable to expect an accrual of 100 patients in a year. Using a 3:1 randomization strategy, 75 will be assigned to active surveillance and 25 to standard care. We estimate that 25% of patients will develop a positive test(13;25;27) and 19 will receive anidulafungin. These numbers should provide sufficient data for a preliminary feasibility evaluation of the preemptive strategy.

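### The 90% power for the gene expression analysis holds only with 30 candidemia cases, a number that 100 patients are unlikely to supply and that leaves few or no cases for testing the signature

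*Protocol*

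**What the plan says.** The RNA Analyses part of Statistical Analyses plans signature development "using an initial cohort of up to 30 persons with candidemia and up to 30 persons with no infection", with as many controls as cases, and adds: "This sample size has 90% power to detect at least a 2-fold change in expression levels", for the 70% of genes that vary least, at an alpha of 0.001. A decision tree is then checked by leaving out one sample at a time. After that, "we will test the generalizability of these profiles on the remaining patients presenting to the intensive care unit".

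The patients come from the trial itself. Secondary Objectives, item 12, takes RNA from the study cohort, and no other source of cases is named. Sample Size states: "Targeted enrollment is 100 adult SICU patients". Exclusion Criteria remove patients with a documented invasive fungal infection at screening, so only new cases count.

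No candidemia rate is stated. The nearest figures are these:

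- Sample Size: "We estimate that 25% of patients will develop a positive test".
- Active surveillance/preemptive therapy group: 81% of patients with invasive candidiasis (IC) test positive at the chosen cut-off.
- Epidemiology of Invasive Candidiasis: experts have advocated prophylaxis "in situations where the rate of IC is expected to approach 10" percent.

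The end point definition of IC covers proven deep tissue infection as well as candidemia, so candidemia is only part of IC. The synopsis uses the verb validate for the gene expression aim, whereas item 12 of the secondary objectives speaks of deriving signatures.

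**The concern.** The Protocol gives power only at the largest cohort it allows for. It does not say how many candidemia cases it expects, or what the power is if fewer occur. Its own figures suggest that 30 is out of reach. A reader of the Protocol would take 90% as a property of this study when it belongs to a cohort the study is unlikely to assemble.

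The validation step has a separate problem that does not depend on any power method. If development may use up to 30 cases and the trial yields 30 or fewer, no case need be left for the later test, and sensitivity cannot be estimated there. At stake are the interpretation of a negative RNA result and whether the synopsis aim can be met in this cohort. No primary endpoint or randomized comparison depends on it.

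**Working it through.** **Inputs from the Protocol.** 100 patients; up to 30 cases and 30 controls; 90% power; a 2-fold change, which is 1 unit on the log2 scale; alpha 0.001, two-sided under the general rule in Statistical Analyses; 25% β-D-glucan positive; 81% sensitivity. Specificity is given as 90% for a single positive test, but in patients with leukemia or myelodysplasia (Preemptive Antifungal Therapy Based on Fungal Biomarkers).

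**1. Rate needed.** 30/100 = 30% with new candidemia.

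**2. Consistency with the plan's test figures.** Thirty cases at 81% sensitivity give 30 × 0.81 = 24.3 positive patients. The plan expects 25 in all. That leaves 25 − 24.3 = 0.7 for false positives among the other 70 patients and for IC without candidemia. The Protocol expects false positives in intensive care (Table 2). At 90% specificity the 70 non-cases alone would add 7, giving 31.3 positives rather than 25.

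Turned round, the infection rate implied by the plan's figures is (0.25 − (1 − specificity)) / (0.81 − (1 − specificity)):

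- Specificity 90%: 0.15/0.71 = 21%.
- Specificity 80% (assumed): 0.05/0.61 = 8%.

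Both count all infection that the test detects, so they are upper limits for candidemia under those inputs.

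**3. Chance of at least 30 cases in 100 (binomial), for assumed rates.** 10%: 2 × 10⁻⁸. 20%: 1%. 25%: 15%. 30%: 54%.

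**4. The plan's 90%.** The gene-level standard deviation (SD) is not stated, so the figure cannot be reproduced independently. It can be used to solve for the SD it implies.

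- Normal approximation: SD = 1 / ((3.291 + 1.282) × √(2/30)) = 0.847.
- Noncentral t, 58 degrees of freedom: 90% power needs a standardised difference of 1.239, so SD = 1/1.239 = 0.807.

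This SD belongs to the most variable gene within the 70% set.

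**5. Power at smaller, assumed case counts.** Same SD, equal groups of n, two-sided alpha 0.001, noncentrality 1.239 × √(n/2), 2n − 2 degrees of freedom:

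| Cases + controls | Noncentral t | Normal approximation |
|---|---|---|
| 5 + 5 | 2.9% | 7.7% |
| 10 + 10 | 17.9% | 25.8% |
| 15 + 15 | 41% | 48% |
| 20 + 20 | 64% | 67% |
| 25 + 25 | 80% | 81% |
| 30 + 30 | 90% | 90% |

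Less variable genes do better. As an illustration, a gene with an assumed SD of 0.5 (standardised difference 2) has about 70% power at 10 + 10.

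**6. Cases left for the later test.** Cases left = cases observed − cases used. With 30 or fewer observed and up to 30 usable, this can be zero. The remaining patients are then all non-cases, which inform specificity only.

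**7. Control ratio.** Controls must be culture-negative and β-D-glucan-negative, and footnote h of the Chart of Study Procedures adds no empiric antifungal therapy. With 25% positive, at most about 100 − 25 = 75 patients qualify. Keeping to 60 arrays but using more controls per case, the t-test power becomes 22% (5 + 55), 55% (10 + 50) and 85% (20 + 40). With 10 cases, 50 controls leave at most 75 − 50 = 25 for the specificity check, against 75 − 10 = 65 under the equal-number rule.

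**The case against.** The wording is conditional: "initial cohort of up to 30 persons with candidemia and up to 30 persons with no infection" is a ceiling, and 90% is the power at that ceiling, not a promise of 30 cases. This stands as a reading, but the Protocol gives no expected count and no power below the ceiling, so the reader is left with 90% alone.

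A reader might infer that the trial will yield 5 to 10 candidemias and that the true power is therefore 3% to 18%. The documents do not support this. They give no candidemia rate, and the 10% figure is a threshold for prophylaxis, not a forecast for this unit. With 90% specificity, the plan's own test figures allow about 21% infected; if all of those were candidemia, power would be about 64% to 67%. The SD is also back-solved, belongs to the most variable gene in the set, and assumes a plain t-test, whereas the plan's figure rests on a cited method that is not at hand.

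Nor does the review show an arithmetic error: 90% at 30 against 30 is neither reproduced nor refuted.

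It would also be too strong to say that nothing is validated. Leave-one-out cross-validation is planned, and item 12 of the secondary objectives already speaks of derivation. What remains is that cross-validation would be the only internal check on sensitivity, while the synopsis promises validation.

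Finally, an equal number of controls is a legitimate design choice. Unequal groups raise per-gene power but create class imbalance for the decision tree and reduce the controls left over. That part is an option only.

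**Conclusion.** The point holds in this form. The stated 90% requires 30 cases, a candidemia rate of about 30% that sits badly with the plan's expectation of 25% test-positive from any cause. Over an assumed range of 5 to 20 cases, equal-group power for the most variable gene in the claimed set is about 3% to 64% by t-test (8% to 67% by normal approximation). These values rest on the assumed case counts, on the SD implied by the plan's own statement and on a two-sided test at 0.001; for less variable genes they are lower limits.

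The limit on the later test follows from the counts alone: with 30 or fewer cases, it can address specificity but not sensitivity once development has used them all. Severity is moderate. This is the last of twelve secondary objectives, in a trial that describes itself as a preliminary feasibility evaluation.

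**What to change.** 1. Replace the single 90% statement with power at 5, 10, 15 and 20 cases. Label the counts as assumptions, and state that 90% requires 30 cases.
2. Describe the RNA aim as exploratory derivation, and bring the synopsis wording into line with secondary objective 12.
3. Limit the step on the remaining patients to specificity, name leave-one-out cross-validation as the only internal check on sensitivity, and defer validation of sensitivity to an external cohort.
4. Optionally, allow more than one eligible control per case within the 60 arrays already planned, noting the class imbalance for the decision tree and the smaller number of controls left for the specificity check.

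Items 1 to 3 are changes of wording and cost a less favourable stated power. Item 4 needs no arrays beyond the 60 planned, but it draws on a pool of at most about 75 eligible controls.
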